### 3.7.2. Laboratory Examination

Lab Examination during the screening visit are as following.

- Blood hematology: counts of red blood cells, white blood cells, neutrophil count, lymphocyte count, platelets, hemoglobin
- Blood biochemistry: serum creatinine, urea nitrogen, uric acid, total carbon dioxide, potassium, sodium and chlorine, alanine aminotransferase, aspartate aminotransferase, albumin, total bilirubin, triglyceride, cholesterol, very low density lipoprotein, high density lipoprotein, low density lipoprotein, calcium, phosphorus, fasting glucose
- Routine urinal assays: urine protein, white blood cells per high power field (WBCs/HPF) and red blood cells per high power field (RBCs/HPF)
- 24-hour UPE rate
- Scoring of histological lesions

### 3.8. Visits

Information to be collected at the visits are summarized in Table 1.

214

**Table 1: Tabulated overview on data collected during the study**

| Phase                              | Screening | Run-in |    |    |   | Treatment period |   |    |    |    |    |    |    |    |    |    |    |    |    |    |     |     |     |     |     |     |     |     |   |  |  |  |  |
|------------------------------------|-----------|--------|----|----|---|------------------|---|----|----|----|----|----|----|----|----|----|----|----|----|----|-----|-----|-----|-----|-----|-----|-----|-----|---|--|--|--|--|
| Visits                             | 1         | 2      | 3  | 4  | 5 | 6                | 7 | 8  | 9  | 10 | 11 | 12 | 13 | 14 | 15 | 16 | 17 | 18 | 19 | 20 | 21  | 22  | 23  | 24  | 25  | 26  | 27  | 28  |   |  |  |  |  |
| Time (week)                        | -14       | -12    | -8 | -4 | 0 | 4                | 8 | 12 | 16 | 20 | 28 | 36 | 44 | 52 | 60 | 68 | 76 | 78 | 86 | 94 | 102 | 110 | 118 | 126 | 134 | 142 | 150 | 156 |   |  |  |  |  |
| Informed consent form              |           | ×      |    |    |   |                  |   |    |    |    |    |    |    |    |    |    |    |    |    |    |     |     |     |     |     |     |     |     |   |  |  |  |  |
| In/exclusion criteria              |           | ×      |    |    |   |                  |   |    |    |    |    |    |    |    |    |    |    |    |    |    |     |     |     |     |     |     |     |     |   |  |  |  |  |
| Medical history/
demography     | ×         |        |    |    |   |                  |   |    |    |    |    |    |    |    |    |    |    |    |    |    |     |     |     |     |     |     |     |     |   |  |  |  |  |
| Height, weight                     | ×         | ×      | ×  | ×  | × | ×                | × | ×  | ×  | ×  | ×  | ×  | ×  | ×  | ×  | ×  | ×  | ×  | ×  | ×  | ×   | ×   | ×   | ×   | ×   | ×   | ×   | ×   | × |  |  |  |  |
| Physical examination               | ×         | ×      |    |    | × |                  |   |    |    |    |    |    |    |    |    |    |    |    |    |    |     |     |     |     |     |     |     | ×   |   |  |  |  |  |
| Vital signs                        | ×         | ×      | ×  | ×  | × | ×                | × | ×  | ×  | ×  | ×  | ×  | ×  | ×  | ×  | ×  | ×  | ×  | ×  | ×  | ×   | ×   | ×   | ×   | ×   | ×   | ×   | ×   | × |  |  |  |  |
| Screening log                      | ×         |        |    |    |   |                  |   |    |    |    |    |    |    |    |    |    |    |    |    |    |     |     |     |     |     |     |     |     |   |  |  |  |  |
| Randomization                      |           |        |    |    | × |                  |   |    |    |    |    |    |    |    |    |    |    |    |    |    |     |     |     |     |     |     |     |     |   |  |  |  |  |
| Blood chemistry        | ×         |        | ×  |    | × | ×                | × | ×  | ×  | ×  | ×  | ×  | ×  | ×  | ×  | ×  | ×  | ×  | ×  | ×  | ×   | ×   | ×   | ×   | ×   | ×   | ×   | ×   | × |  |  |  |  |
| Hematology                         | ×         |        | ×  |    | × | ×                | × | ×  | ×  | ×  | ×  | ×  | ×  | ×  | ×  | ×  | ×  | ×  | ×  | ×  | ×   | ×   | ×   | ×   | ×   | ×   | ×   | ×   | × |  |  |  |  |
| Urinary analysis                   | ×         |        | ×  |    | × | ×                | × | ×  | ×  | ×  | ×  | ×  | ×  | ×  | ×  | ×  | ×  | ×  | ×  | ×  | ×   | ×   | ×   | ×   | ×   | ×   | ×   | ×   | × |  |  |  |  |
| 24-hour urine protein  | ×         |        | ×  |    | × | ×                | × | ×  | ×  | ×  | ×  | ×  | ×  | ×  | ×  | ×  | ×  | ×  | ×  | ×  | ×   | ×   | ×   | ×   | ×   | ×   | ×   | ×   | × |  |  |  |  |
| Diet education                     | ×         | ×      | ×  | ×  | × | ×                | × | ×  | ×  | ×  | ×  | ×  | ×  | ×  | ×  | ×  | ×  | ×  | ×  | ×  | ×   | ×   | ×   | ×   | ×   | ×   | ×   | ×   | × |  |  |  |  |
| Study drug dispensation            |           |        |    |    |   | ×                | × | ×  | ×  | ×  | ×  | ×  | ×  | ×  | ×  | ×  | ×  | ×  |    |    |     |     |     |     |     |     |     |     |   |  |  |  |  |
| Concomitant medications            | ×         | ×      | ×  | ×  | × | ×                | × | ×  | ×  | ×  | ×  | ×  | ×  | ×  | ×  | ×  | ×  | ×  | ×  | ×  | ×   | ×   | ×   | ×   | ×   | ×   | ×   | ×   | × |  |  |  |  |
| AEs/SAEs                           |           |        | ×  | ×  | × | ×                | × | ×  | ×  | ×  | ×  | ×  | ×  | ×  | ×  | ×  | ×  | ×  | ×  | ×  | ×   | ×   | ×   | ×   | ×   | ×   | ×   | ×   | × |  |  |  |  |
| Endpoints                          |           |        |    |    |   | ×                | × | ×  | ×  | ×  | ×  | ×  | ×  | ×  | ×  | ×  | ×  | ×  | ×  | ×  | ×   | ×   | ×   | ×   | ×   | ×   | ×   | ×   | × |  |  |  |  |

215

216

217

218

1. Including: serum creatinine (CR), urea nitrogen (BUN), uric acid (UA), total carbon dioxide (tCO2), potassium (k), sodium (NA) and chlorine (CL), alanine aminotransferase (ALT), aspartate aminotransferase (AST), albumin (ALB), total bilirubin (T-Bil), triglyceride (TG), cholesterol (Chol), very low density lipoprotein (VLDL), high density lipoprotein (HDL), low density lipoprotein (LDL), calcium (CA), phosphorus (P), glucose (Glu). It is necessary to remind the patient at the first visit that blood should be taken on a fasting status at the next visit.
2. It is necessary to remind the patient to take a 24-hour urine sample at the next visit at the previous visit

## **4. General Statistical Considerations**

### **4.1. General Principles**

The analysis conducted will follow the relevant standard operating procedures (SOP). Programs, logs, and output will be reviewed for accuracy according to the SOPs for programming and quality control. Descriptive analysis of the data will be performed using summary statistics for categorical and quantitative (continuous) data. Continuous data will be described by the number of non-missing values, median, mean, standard deviation, minimum, and maximum as well as lower and upper quartiles. If not specified, the mean and median are retained 1 decimal place more than the original data, and the standard deviation is retained 1 decimal place more than the mean, but all statistics are rounded to no more than 3 decimal places. Frequency tables (the number of cases, percentages rounded to retain 1 decimal place) will be generated for categorical data. Selected continuous variables will be categorized in a clinically meaningful way or by quartiles of the distribution. In addition, if sparse cells (i.e. count<10 for variables) are identified during the analysis, the sparse cells may be combined into other meaningful categories, excluded from analysis, or left as they are. Decisions will be made by the study team at the time sparse cells are identified.

### **4.2. Handling of Lost to Follow Up and Premature Discontinuation**

The distribution of subjects will be presented including the number and percentage of subjects enrolled, screening failure, lost to follow up, discontinuation, and completing the study. For the subjects who failed screening, the number and percentage of subjects for each reason will be clarified and summarized, such as inclusion criteria not met / exclusion criteria met, patient decision, physician decision (medical reason, unable to participate / internal hospital guidelines) and others. The detailed reasons for screening failure of each subject will be presented in the lists.

For the subjects who are lost to follow up or prematurely discontinue the trial, their main reasons will be clarified and summarized, such as patient decision, physician decision, patient voluntary withdrawal, AE, other reasons. The detailed reasons for loss to follow up or premature discontinuation of each subject will be presented in the lists.

### **4.3. Handling of Missing Data**

For primary and secondary endpoints, missing data will be treated as missing, and no imputations will be performed.

Counts of missingness will be reported in descriptive analysis of categorical variables, and percentages of the non-missing categories will be based on all values. For continuous variables, the number of non-missing values as well as missing values will be reported, but descriptive summaries will be based on the number of non-missing values.

### **4.4. Multiplicity Adjustment**

For the primary analysis, a two-sided p value of <0.025 was regarded as statistically significant. For the secondary and safety analyses, no multi-test adjustment was employed, and a two-sided p value of <0.05 was regarded as statistically significant. The outcomes are clearly categorized by degree of importance (primary, secondary) and a limited number of subgroup analyses are pre-specified.

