#### 7.4 Sample size

The sample size is estimated before the study with the use of nQuery Advisor software. Our preliminary study of IgA nephropathy showed that the three-year rate of the primary endpoint (doubling of serum creatinine, end-stage renal disease, and death) among patients with IgA nephropathy taking RAS inhibitors was 36%. It is estimated that MMF treatment will reduce this rate to 16%. Thus, the enrollment of 76 per group will provide the study with a statistical power of 80% at a two-sided significance level of 0.05. Considering 10% of participants lost to follow-up over 3 years, the final sample size was 84 per group.

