## 3.4. Primary Outcomes

There are two primary outcomes.

1. The time to the first event of the composite outcomes, including:
  - a doubling of serum creatinine, defined as serum creatinine doubled over the baseline and confirmed by another measurement at least four weeks apart; or
  - onset of end stage kidney disease, defined by the need for maintenance dialysis or renal transplantation or kidney failure (defined as  $\text{eGFR} < 15 \text{ ml/min/1.73m}^2$  and need for dialysis or renal transplant, but renal replacement therapy is not available or patients refuse to receive renal replacement therapy); or death due to kidney or cardiovascular cause.
2. The time to progression of CKD, defined by a sustained  $\geq 30\%$  decrease in eGFR and to a level of  $< 60 \text{ ml/min/1.73m}^2$  if the baseline eGFR was  $\geq 60 \text{ ml/min/1.73m}^2$ , or  $\geq 50\%$  decrease in eGFR if the baseline eGFR was  $< 60 \text{ ml/min/1.73m}^2$ . The CKD progression endpoints were also verified by another measurement at least four weeks apart.

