## **6.3. Efficacy Analyses**

### **6.3.1. Main Analyses of the Primary Outcomes**

- The number of the composite outcome (primary outcome 1) and its components by each treatment group in ITT.
- The number of disease progression (primary outcome 2) by each treatment group in ITT.
- Kaplan-Meier curves of cumulative survival rates of the two primary outcomes by two treatment groups in ITT.
- To perform log-rank tests on the two primary outcomes between the two treatment groups in ITT. A p-value of 0.025 will be regarded as statistically significant.
- Estimate the hazard ratios (and 95% confidence intervals) of the treatment for the two primary outcomes, respectively, using the Cox proportional hazard models, with and without covariate adjustment. The adjusting covariates include age, sex, BMI, SBP, eGFR, logarithm of UPE rate and individual Oxford MEST-C scores at baseline.

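### SAP 4.4 and 6.3.1 hold both primary outcomes to a flat 0.025, a valid but needlessly conservative Bonferroni split; Holm keeps the 0.05 bound and adds power on the second outcome

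*Combined protocol and SAP*

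**What the plan says.** SAP 3.4 states "There are two primary outcomes": a composite of creatinine doubling, end-stage kidney disease and death from kidney or cardiovascular cause (outcome 1), and progression of CKD defined by eGFR loss (outcome 2).

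SAP 4.4 sets the threshold: "For the primary analysis, a two-sided p value of <0.025 was regarded as statistically significant". SAP 6.3.1 plans "To perform log-rank tests on the two primary outcomes between the two treatment groups in ITT" and adds "A p-value of 0.025 will be regarded as statistically significant". Neither section gives a hierarchy, a step-down, a transfer of alpha or a requirement to win on both. The SAP does not name Bonferroni or state a family-wise level, but 2 x 0.025 = 0.05.

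For estimation, 6.3.1 asks the analyst to "Estimate the hazard ratios (and 95% confidence intervals) of the treatment for the two primary outcomes, respectively". These are 95% intervals, not 97.5%.

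Protocol 7.4 sizes the trial on one endpoint rate, 36% versus 16% at three years: "the enrollment of 76 per group will provide the study with a statistical power of 80% at a two-sided significance level of 0.05". With 10% loss this becomes 84 per group.

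**The concern.** Under the flat rule, each outcome must reach 0.025 whatever the other shows. Once one null hypothesis has been rejected, only one remains, and testing it at 0.05 cannot take the family-wise error above 0.05. The plan leaves that alpha unused.

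Take p = 0.01 on CKD progression and p = 0.04 on the composite. The plan declares the composite not significant; Holm declares it significant, with the same family-wise guarantee. At stake is whether the trial can claim its second primary outcome. Whether it can claim any primary outcome is unaffected.

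**Working it through.** **Inputs.** From the documents: two primary outcomes (SAP 3.4); 0.025 two-sided for each (SAP 4.4, 6.3.1); 36% versus 16%, 76 per group, 80% power at two-sided 0.05 (protocol 7.4); 1:1 allocation (protocol 7.5). Assumed, because the documents are silent: the effect on outcome 2 and the correlation rho between the two test statistics.

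**1. The plan's own figure.** Pooled rate 0.26; null SD = sqrt(2 x 0.26 x 0.74) = 0.620; alternative SD = sqrt(0.36 x 0.64 + 0.16 x 0.84) = 0.604; difference 0.20.

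n = [(1.960 x 0.620 + 0.842 x 0.604)/0.20]^2 = 74.3, so 75 per group against 76 stated. Reproduced. 76 x 1.1 = 83.6 gives the 84.

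**2. Power at 76 per group.** Power = Phi[(0.20 x sqrt(76) - z x 0.620)/0.604].
- At 0.05 (z = 1.960): Phi(0.874) = 80.9%.
- At 0.025 (z = 2.241): Phi(0.585) = 72.1%.

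**3. Error control.** Under Holm:
- Both nulls true: an error requires the smaller p below 0.025, so the probability is at most 0.025 + 0.025 = 0.05, exactly as now.
- One null true: an error requires that outcome's p below 0.05, so the probability is at most 0.05.

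Neither step uses the correlation. Holm's first step is the present rule, so it never rejects less.

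**4. Hand check at rho = 0, same effect on both outcomes.** Treat each statistic as normal with mean 2.241 + 0.585 = 2.826 and unit variance. Power is then 72.1% at 0.025 and 80.7% at 0.05 (the unit-variance simplification accounts for 80.7 rather than 80.9). The probability that p falls between 0.025 and 0.05 is 0.807 - 0.721 = 0.086.
- Per outcome: 0.721 + 0.086 x 0.721 = 0.783.
- Both: 0.807^2 - 0.086^2 = 0.644, against 0.721^2 = 0.520 now.

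**5. Simulation over rho (4 million draws, same assumption).**

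| rho | Per outcome, flat to Holm | Both, flat to Holm | At least one, either rule | Error, both nulls true, either rule |
|---|---|---|---|---|
| 0 | 72.1% to 78.3% | 52.0% to 64.4% | 92.2% | 4.94% |
| 0.5 | 72.1% to 77.2% | 58.2% to 68.6% | 85.9% | 4.66% |
| 0.8 | 72.1% to 76.5% | 63.5% to 72.2% | 80.7% | 4.01% |
| 0.9 | 72.1% to 75.9% | 66.0% to 73.7% | 78.1% | 3.63% |

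The gain is 3.8 to 6.2 points per outcome and 7.7 to 12.4 points for both.

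**6. Different effects on the two outcomes.** Log-rank simulations, 84 per group, 10% loss, exponential times, outcome 1 at 36% versus 16% and nested in outcome 2. The rates for outcome 2 are assumptions.
- 45% versus 22%: outcome 1 76.0% to 81.6%; both 72.0% to 80.2%.
- 40% versus 18%: outcome 1 76.2% to 81.0%; both 73.8% to 80.3%.
- 46% versus 26%: outcome 1 74.8% to 78.0%; both 60.9% to 70.2%.
- 42% versus 26%: outcome 1 75.3% to 76.1%. 45% versus 30%: 75.6% to 76.4%. 42% versus 30%: a gain of 0.2 points. In these three, outcome 2 gains about 9-11 points.

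The chance of at least one win does not change, so the two single-outcome gains add up to the gain for both. At 46% versus 26%, outcome 2 therefore gains (70.2 - 60.9) - (78.0 - 74.8) = 6.1 points.

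**7. One null true.** With a real effect on outcome 1 (step 4) and none on outcome 2, error on outcome 2 rises from 2.5% to 4.3% at rho = 0 and 3.8% at rho = 0.9. With an overwhelming effect on outcome 1 it reaches 5.0%.

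**The case against.** The strongest reply is that nothing here is wrong. The SAP names two primary outcomes, fixes a threshold and applies it consistently; family-wise error is at most 5%. Preferring Bonferroni to Holm is a legitimate, stricter choice. That stands: this is an efficiency improvement, and a reader who infers that the multiplicity rule fails would be mistaken.

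Other tempting inferences also go too far:
- *Holm makes the trial more likely to succeed.* Only if success requires a particular outcome or both. The chance of at least one win is identical, and the documents do not define success.
- *The outcomes overlap, so the second threshold is needless.* They probably do overlap: if eGFR varies roughly inversely with creatinine, a doubling is about a 50% fall. But Holm's validity does not depend on overlap, and in step 5 higher correlation shrinks the gain. Nesting is also incomplete, since death counts only in outcome 1.
- *It costs nothing.* It costs no patients and does not raise the family-wise bound. But error on a single true null can double within that bound, and Holm has no simple matching simultaneous intervals. The second loss is small here, because the SAP plans 95% intervals and has no Bonferroni-matched ones to give up.
- *It restores the stated 80% power.* Sizing at 0.05 and testing at 0.025 is a separate mismatch. Under step 5 each outcome stays below 80%. Holding 80% at a flat 0.025 would need 91 per group, or 102 after 10% loss.

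Timing is a fair worry too. SAP section 3 describes recruitment and randomization in the past tense, and the trial is open-label. Relaxing a primary threshold once results are known would not be credible.

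**Conclusion.** The point holds as an efficiency improvement to a valid plan. Holm never rejects less than the flat rule and has the same 0.05 bound under any dependence.

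The gain falls only on the second outcome, and its size rests on quantities that the documents do not give. With the 36% versus 16% effect on both outcomes at 76 per group, it is about 4-6 points per outcome and 8-12 for both. If outcome 2 has a weaker effect (46% versus 26% down to 42% versus 30%), outcome 1 gains only about 0-3 points and most of the benefit goes to outcome 2, about 6-11 points. The documents support neither a claim that the present rule is in error nor a claim that Holm raises the chance of at least one significant primary outcome.

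**What to change.** In SAP 4.4 and 6.3.1, replace the flat threshold with Holm: the smaller of the two primary log-rank p-values is tested at two-sided 0.025; if it is significant, the other is tested at two-sided 0.05; if it is not, neither outcome is significant. State the family-wise level of 0.05 explicitly. Add that the planned 95% intervals are for each outcome separately and are not simultaneous intervals matched to the Holm decisions.

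The cost is about one sentence in each section, plus the two downsides named above; no patients and no new data. Make and date the change before database lock and any unblinded look. Protocol 7.12 leaves the SAP open until lock, and SAP 3.3 keeps the statistical analysis group unaware of assignment, so this is feasible if neither point has been passed. If the data have been unblinded, keep the existing rule. Deal with the sample-size alpha mismatch separately.

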## **5. Analysis Sets**

### **5.1. Intention-to-test Set (ITTs)**

ITT includes all subjects randomized to treatment. The ITT set will be the set for all efficacy analyses.

### **5.2. Safety Set (SS)**

SS is a subset of ITT. It consists of ITT participants excluding the ones without taking any study medication or having no record of follow up after randomization. SS will be used for the safety analysis.

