## **7.2 Study drug**

### **(1) Drug information**

- Drug: Mycophenolate mofetil (MMF)
- Formulation: Mycophenolate mofetil tablets 0.25g/tablet
- Manufacturer: Hangzhou Zhongmei Huadong Pharmaceutical Co., Ltd

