### Analysis sets

1. ITTs (Intention-to-test set): All enrolled subjects who sign the informed consent and undergo randomization. ITTs will be used for all efficacy analyses
2. SS (Safety set): All enrolled patients who have used the study drug. The SS set will serve as the primary analysis population for all safety outcomes.

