### **Collection**

After enrollment into the study, all non-serious adverse events (AE) must be documented on the AE Report Form or in the CRF/EDC system and forwarded to the sponsor within 7 calendar days of awareness. All serious AEs (SAE) must be documented and forwarded immediately (within one business day of awareness). For each AE, the investigator or a delegate must assess and document the seriousness, duration, relationship to product, action taken and outcome of the event.

If a pregnancy occurs during the study, although it is not a serious adverse event itself, it should be documented and forwarded to the sponsor within the same time limits as a serious adverse event. The result of a pregnancy will be followed-up according to applicable SOPs. Any data on abnormal findings concerning either the mother or the baby will be collected as adverse events.

All drug related events must be documented on the product related CRF form or in the CRF / EDC system and also on the PTC form(s). Incidents must be forwarded to the study initiator and funder within 24 hours (immediately) and other events must be forwarded within 7 calendar days of awareness. Products suspected of defects should be retained for recycling and returned to the sponsor for further inspection and verification

The documentation of any AE/SAE/drug related events ends with the completion of the observation period of the patient. However, any AE/SAE - regardless of the relationship and the seriousness - occurring within  $30 \pm 7$  days after the last use of MMF within the study period has to be documented and forwarded to the sponsor within the given timelines, even if this period goes beyond the end of observation.

As long as the patient has not used any MMF within the frame of the study AEs /SAEs do not need to be documented as such in this observational study. However, they are part of the patient's medical history.

For any serious product-related AE occurring after study end, the standard procedures that are in place for spontaneous reporting has to be followed.

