## 3.2. Study Drug

### Drug information

- Drug: Mycophenolate mofetil
- Formulation: Mycophenolate mofetil tablets 0.25g/tablet
- Manufacturer: Hangzhou ZhongmeiHuadong Pharmaceutical Co., Ltd

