## 3.7. Safety Endpoints

### 3.7.1. Adverse Events

#### (1) AEs/SAEs

AEs/SAEs occurred during the study period from the first application of MMF to 30±7 days after the last use of MMF will be analyzed and summarized.

**Adverse event (AE):** Any untoward medical occurrence in a patient with the use of a medical product and which does not necessarily have to have a causal relationship (association) with this product. An AE can therefore be any unfavorable and unintended sign (including an abnormal laboratory finding), symptom, or disease temporally associated with the use of the study device, whether or not related to the product.

**Adverse Reaction (AR):** is defined as a response to the study device which is noxious and unintended. An AR is any AE judged as having a reasonable suspected causal relationship to the study device. The assessment of the causal relationship between an AE and the use of the study device is a clinical decision by the investigator based on all available information at the time of the completion of the CRF. The assessment is based on the question whether there was a "reasonable causal relationship" to the study device in question. Possible answers are "yes" or "no".

**Serious adverse event/serious adverse reaction:** an adverse event (AE) or adverse reaction (AR) is serious if it:

- results in death,
- is life-threatening
- requires inpatient hospitalization or prolongation of existing hospitalization.
- results in persistent or significant disability or incapacity
- is a congenital anomaly, birth defect or fetal mental impairment
- is medically significant: Medical and scientific judgment should be exercised in deciding whether an AE/AR may be considered serious (due to an important medical event) because it jeopardizes the health of the patient or may require intervention to prevent another serious condition (death, a life-threatening condition, hospitalization or persistent or significant disability).

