### **6.4. Safety Analysis**

The analysis of safety endpoints will be performed on the SS. For safety analysis, no formal hypothesis testing will be performed. Descriptive analysis will be performed to summarize safety events. Serious adverse events and adverse events will be summarized as the number of events and the number (%) of patients experiencing at least one event. Differences in the proportions of patients experiencing at least one event will be tested using Fisher's exact test.

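### The Safety Set and the adverse-event window are defined by MMF use, so control patients have neither, and the planned between-arm comparison of adverse events cannot be made as written

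*Combined protocol and SAP*

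**What the plan says.** **Who is analysed.** Protocol 7.12 (Analysis sets) reads "SS (Safety set): All enrolled patients who have used the study drug". Protocol 7.2 and SAP 3.2 each list one study drug, MMF; the SAP entry is "Formulation: Mycophenolate mofetil tablets 0.25g/tablet". SAP 5.2 describes the set differently: "It consists of ITT participants excluding the ones without taking any study medication or having no record of follow up after randomization". The SAP does not say what counts as study medication.

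**Which events are analysed.** SAP 3.7.1 covers "AEs/SAEs occurred during the study period from the first application of MMF to 30±7 days after the last use of MMF".

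**Which events are collected.** Protocol section 9 (Collection) opens by requiring all adverse events after enrolment to be documented. Protocol 7.7 (Safety endpoints) has events in the study period recorded, and Table 1 marks adverse events at every visit from Visit 3 to Visit 28. None of these is restricted by arm. Later in the same Collection section comes the waiver: "As long as the patient has not used any MMF within the frame of the study AEs /SAEs do not need to be documented".

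**What is done with them.** SAP 6.4 runs the safety analysis on the Safety Set. It first says there will be no formal testing, then plans a test: "Differences in the proportions of patients experiencing at least one event will be tested using" Fisher's exact test. SAP 4.4 sets a two-sided 0.05 threshold for safety analyses. SAP 6.4.2 compares laboratory results by treatment group.

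**The concern.** The trial compares MMF plus supportive care with supportive care alone. A patient who is assigned to control and stays on it never takes MMF. Such a patient is outside the protocol's Safety Set, has no start or end to the SAP's event window, and falls under the documentation waiver if that sentence is read literally. The harm of adding MMF can only be judged against the control arm, so these rules remove the comparator from the one analysis meant to assess it.

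Two further things are at stake. First, the trial is open-label. A site that knows a patient is a control and holds an explicit waiver may record fewer events, and analysis cannot repair that. Second, the protocol continues event documentation to the end of each patient's observation, but the SAP window stops soon after the last MMF dose. Events collected later in the MMF arm would be left out. Malignancy, which both documents list as an event of special concern, may appear late.

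**Working it through.** The plan gives no adverse-event rates and no safety sample size, so there is no safety figure to reproduce. Arm sizes come from protocol 7.4.

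1. **Arm size.** Inputs: 36% vs 16%, two-sided 0.05, 80% power. With pooled variance, n = [1.960 × √(2 × 0.26 × 0.74) + 0.842 × √(0.36 × 0.64 + 0.16 × 0.84)]² / 0.20² ≈ 74.3, so 75 per group against the stated 76. Then 76 × 1.10 = 83.6, rounded to the stated 84. The plan's figure reproduces; it is used here only to fix 84 vs 84.

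2. **Rules applied literally.**

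| Rule | MMF arm | Control arm |
|---|---|---|
| Protocol Safety Set | MMF users | 0 of 84 |
| SAP 5.2 Safety Set | takers of study medication with follow-up | 0 of 84 if study medication means MMF |
| SAP 3.7.1 window | first to last MMF use, plus 30±7 days | undefined |
| Section 9 waiver | does not apply once MMF is used | documentation not required |

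   With no controls, the Fisher table has an empty row. Only one table fits the margins, so p = 1.0 and the odds ratio is undefined, whatever the MMF count (checked at 0, 20, 42 and 84 of 84).

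3. **Controls kept in the set, MMF-based event rules unchanged.** Suppose losartan counts as study medication under SAP 5.2. Control events are then 0 of 84 by rule. With equal arms and all k events in one of them, the two-sided Fisher p is 2 × C(84, k) / C(168, k):
   - k = 5: p = 0.059
   - k = 6: p = 0.028

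   Six MMF patients with any event would cross the 0.05 threshold purely because of how events are counted.

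4. **Length of the MMF window.** The course is 12 months plus at least 6, so the minimum is 18 months, or 78 weeks. Table 1 marks the last dispensing at Visit 18, also week 78. Follow-up ends at week 156.
   - Window end = 78 + 30/7 = 82.3 weeks (81.3 to 83.3 for 23 to 37 days).
   - Share not analysed = (156 − 82.3)/156 = 47% (46.6% to 47.9%).
   - Each further week of MMF lowers this by 1/156, about 0.6 percentage points. A patient who stops early has a shorter window and a larger unanalysed share.

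5. **With a common set and window.** The table has up to 84 vs 84 patients and the test can be run. For assumed control vs MMF event rates, Fisher power at 0.05 is 15% for 5% vs 10%, 51% for 5% vs 15%, and 82% for 5% vs 20%. The comparison is feasible but can detect only large differences.

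**The case against.** **Safety data exist for controls.** A reader might infer that the control arm will have no safety data. The documents do not support that. The opening of the Collection section, protocol 7.7 and Table 1 all call for event recording without regard to arm, blood tests are scheduled for everyone, and SAP 6.4.2 compares laboratory results by group. The waiver removes a duty; it does not forbid recording. This objection stands. The defect is a contradiction about collection, together with analysis rules that leave controls out.

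**The waiver may concern timing only.** The sentence goes on to treat the events as medical history, so it could be meant for the period before a patient's first MMF dose. It also calls this randomised trial observational, which suggests carried-over text. That reading is possible, but the words cover a patient who never takes MMF equally well, and nothing else in the documents settles it.

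**Losartan may count as study medication.** SAP section 2 frames the comparison as MMF with losartan against losartan alone, and every participant receives losartan. SAP 5.2 alone is therefore not decisive. The reading does not rescue the plan, however. Table 1 dispenses study drug only at Visits 6 to 18 while losartan continues throughout, and the protocol Safety Set and the SAP window remain tied to MMF.

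**The safety analysis is descriptive.** SAP 6.4 does say so, which lowers the weight of the Fisher p-value. But a descriptive comparison also needs a control denominator and a shared window.

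**A size of bias might be inferred.** A reader might set 36 months of control events against about 19 months of MMF events and quote a spurious advantage for MMF. No passage prescribes that mixture, no event rate is given to base it on, and it cannot hold together with controls leaving the set.

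**Conclusion.** The point holds as a defect in the analysis rules and an internal contradiction on collection, and it needs correcting before the safety analysis is run. Applied as written, the protocol Safety Set and the SAP event window give control patients (84 planned) no place in the adverse-event comparison of SAP 6.4. If only the set is relaxed, the control count is zero by rule and the result is an artefact.

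The strongest evidence is the protocol's Safety Set definition, the SAP window and the section 9 waiver; the SAP 5.2 sentence adds to it but turns on an undefined term. The 47% of follow-up left unanalysed in the MMF arm assumes that MMF stops at week 78, the minimum course. It falls with longer treatment and rises with early stopping. The documents do not show that control events will go unrecorded, only that sites have been given conflicting instructions.

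**What to change.** - **Safety Set (protocol 7.12, SAP 5.2):** all randomised patients with post-randomisation follow-up, analysed by treatment received (any MMF vs none). Use one definition in both documents, and define study medication.
- **Event window (SAP 3.7.1, 6.4):** randomisation to week 156 in both arms for the between-arm comparison. Keep first MMF dose to 30 days after the last as a supportive on-treatment summary for the MMF arm.
- **Collection (protocol section 9):** delete the waiver, or limit it to the time before randomisation. If it is limited, reconcile it with the adverse-event marks at the run-in visits in Table 1.
- **Status of the test (SAP 4.4, 6.4):** state whether the Fisher p-values are descriptive or judged at 0.05; at present the SAP says both.

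The cost is wording in these sections. Table 1 already schedules event recording at every post-randomisation visit, so no visit is added. One loss cannot be repaired this way: control events already left unrecorded under the waiver are gone. The sponsor should establish how sites applied that sentence and report any gap as a limitation.
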